## Abstract

**Introduction:**

Distal radius fractures are the most common fractures seen in the emergency department in children in the USA. However, no established or standardised guidelines exist for the optimal management of completely displaced fractures in younger children. The proposed multicentre randomised trial will compare functional outcomes between children treated with fracture reduction under sedation versus children treated with simple immobilisation.

**Methods and analysis:**

Participants aged 4–10 years presenting to the emergency department with 100% dorsally translated metaphyseal fractures of the radius less than 5 cm from the distal radial physis will be recruited for the study. Those patients with open fractures, other ipsilateral arm fractures (excluding ulna), pathologic fractures, bone diseases, or neuromuscular or metabolic conditions will be excluded. Participants who agree to enrol in the trial will be randomly assigned via a minimal sufficient balance algorithm to either sedated reduction or in situ immobilisation. A sample size of 167 participants per arm will provide at least 90% power to detect a difference in the primary outcome of Patient-Reported Outcomes Measurement Information System Upper Extremity computer adaptive test scores of 4 points at 1 year from treatment. Primary analyses will employ a linear mixed model to estimate the treatment effect at 1 year. Secondary outcomes include additional measures of perceived pain, complications, radiographic angulation, satisfaction and additional procedures (revisions, refractures, reductions and reoperations).

**Ethics and dissemination:**

Ethical approval was obtained from the following local Institutional Review Boards: Advarra, serving as the single Institutional Review Board, approved the study (Pro00062090) in April 2022. The Hospital for Sick Children (Toronto, ON, Canada) did not rely on Advarra and received separate approval from their local Research Ethics Board (REB; REB number: 1000079992) on 19 July 2023. Results will be disseminated through publication in peer-reviewed journals and presentations at international conference meetings.

**Trial registration number:**

NCT05131685.

STRENGTHS AND LIMITATIONS OF THIS STUDYThis trial will leverage the Infrastructure for Musculoskeletal Pediatric Acute Care Clinical Trials consortium, recruiting participants from over 34 clinical sites across the USA and Canada.The randomised pragmatic study design will mirror typical clinical visits and leverage electronic consent and data collection, minimising the burden on surgeons and participants.Centralisation of study activities through clinical and data coordinating centres will increase efficiency in identifying, consenting and following participants.Participants will be randomised centrally by the Data Coordinating Center via a minimal sufficient balance algorithm to prevent serious imbalances between treatment arms on centre, age and sex.This is an open unmasked trial as participants and surgeons are not blinded to individual interventions at their sites.

## Introduction

 Distal radius fractures (DRFs) make up 20–25% of all paediatric fractures^1 2^ and are the most common fractures seen in the emergency department in children in the USA.^3^ The available evidence on DRF reduction/non-reduction is based on case series, observational comparisons and expert opinions. Displaced, bayonetted metaphyseal DRFs have historically been treated with attempts at closed reduction (under conscious sedation or anaesthesia). This approach was supported by retrospective studies and consensus opinion that anatomical alignment was necessary for functional range of motion.^4 5^ Furthermore, it is unsettling for physicians and families to see bones overlapped on a radiograph when a reduction procedure can be completed in a straightforward fashion. However, simple immobilisation without attempted reduction has been reported for management of DRFs in children under age 10.^6^ This approach is conceptually supported by the fracture’s proximity to the distal radial physis and the remaining growth of the child, which provides significant remodelling potential and can allow for improvement of malalignment as the child grows.^6 7^ There is a paucity of literature comparing reduced to non-reduced fractures to guide management. No established or standardised guidelines exist for these types of fractures.

Surveys have identified widely discrepant recommendations and high practice variation for treatments for overlapped DRF patterns.^8^ In the UK, surgical pin fixation is used routinely for fears of reisplacement.^9 10^ In the USA, identical injuries would undergo different treatment depending on the surgeon’s background (hand surgeon, paediatric orthopaedist, general orthopaedist or orthopaedic traumatologist), and depending on the practice model (public vs private).^11^

Although existing studies provide preliminary data to support clinical management, the studies lack a control population for comparison, are retrospective, lack randomisation, have variable follow-up times and/or have no standard definitions of outcomes. In addition, the studies used radiographic or non-validated outcome measures to make conclusions, limiting their utility in identifying optimal management. Previous trials of distal radius fractures in children often involved surgical fixation, a focus on long arm versus short arm casts, and none had patient-reported outcomes.^1012^,^15^

Thus, the proposed trial will compare the effectiveness of alignment under sedation/anaesthesia versus in situ immobilisation for management of overriding DRFs in children, providing critical data regarding optimal management of this common fracture. Therefore, this study’s primary question is the following: does anatomic reduction under sedation/anaesthesia of DRF result in different patient outcomes at 1 year compared with immobilisation without attempted reduction? Secondary objectives include (1) quantifying differences in perceived pain, (2) evaluating cosmetic differences, (3) quantifying differences in complication rates, (4) estimating cost differences, (5) determining patient and parent satisfaction and return to activities and (6) evaluating long-term functional differences.

## Method and analysis

### Study design

This study is a multicentre, parallel randomised (1:1) controlled trial evaluating two common treatments for completely displaced, overriding metaphyseal DRFs. Designed to avoid large interruptions in busy orthopaedic practices or emergency departments, the practical design will mirror clinical care. In-person assessments will be conducted at baseline, 6 weeks and 3 months to include physical exams, questionnaires and radiographic or other imaging assessments. Anterior-posterior and lateral radiographs of the wrist and forearm will be obtained, and complications will be tracked. Subsequent collection of questionnaires at 6 months, 1 year, 2 years and 3 years will leverage electronic surveys to reduce participant and clinical staff burden (figure 1). Additional radiographs will be collected for any participant returning to the clinic during the follow-up period. Participants will complete all study activities 3 years after fracture.

**Figure 1 F1:**
[figure not shown]
Study schema.

Given the nature of the intervention, it is not practical for patients or treating surgeons to be blinded to the randomised treatment group. In order to reduce bias from the lack of blinding to treatment, the treating surgeon will not provide primary outcome follow-up data on the patient nor participate in the final analysis. Patient-reported outcome surveys will be administered by separate personnel from the care team, and follow-up data will be collected directly from the patient and family.

The Distal Radius Interventions for Fracture Treatment trial is governed by executive and steering committees. The executive committee is responsible for overall study leadership and oversight (principal investigator: [name]). The steering committee includes all members of the executive committee and additional physician-representatives from participating clinical centres and the Data Coordinating Center (DCC). The steering committee is responsible for the conduct of the trial and provided scientific input on study design and implementation. The DCC, led by the Duke Clinical Research Institute, will coordinate data management, data monitoring and statistical analyses. The Clinical Coordinating Center (CCC), located at Lurie Children’s Hospital, will provide overall project management, regulatory, training and monitoring support. Centralised recruiting and dedicated follow-up by research personnel at the CCC, along with remuneration for visit completion, will facilitate enrolment and minimise attrition.

### Participants

Patients will be recruited from the emergency departments or the orthopaedic clinics in the Infrastructure for Musculoskeletal Pediatric Acute Care Clinical Trials (Distal Radius Interventions for Fracture Treatment (DRIFT) trial: study protocol for a multicentre randomised clinical trial in children) consortium. The Infrastructure for Musculoskeletal Pediatric Acute Care Clinical Trials consortium includes 34 hospitals across the USA and Canada, recruited from members of the Pediatric Orthopaedic Society of North America. Information on participating sites can be found on the ClinicalTrials.gov record (online supplemental file 1). Patients aged 4–10 inclusive who present to the emergency department or the orthopaedic clinics with 100% dorsally translated metaphyseal fractures of the radius will be assessed for inclusion by site staff trained in the protocol (AO PCCF classification 23-M/3.1 and 23r-M/3.1 are included).^16^ If the family is interested in learning more about the study, orthopaedic or emergency department representatives will provide the family with an iPad so they can view a short informational video (https://drift-study.digitrial.com) and read more about the study. If the family is interested, they can discuss the study with the CCC via videoconference. The CCC is staffed by research personnel and will be available 24 hours/day to facilitate enrolment, discuss study information and consent process (see online supplemental files 2; 3), and answer any questions with patient/family in real time. If the family is interested in enrolling, either the orthopaedic attending/representative or the CCC will instruct them on how to begin the e-consent process. The family will then consent via the clinic iPad or personal device and only one parent/guardian is required for consent. If the child is between the ages of 7 and 10 years old, assent is obtained. Once the e-consent form is completed, and the assent form if applicable, the family will be provided a copy of the form. If the patient and family decline study participation, the patient will be treated per the treating physician’s regular care recommendation. If consent cannot be obtained from a parent or legal representative, then the patient is not approached for participation. Children and families who are approached for enrolment and decline will be added into a screening log. The screening log will include demographic information including age, sex, race, ethnicity, who approached the patient, and, if they decline participation, reason why they declined and their ultimate treatment.

Inclusion and exclusion criteria are detailed in box 1.

Box 1DRIFT inclusion and exclusion criteriaInclusion criteriaProvision of signed and dated informed consent form by parent or legal guardian.Stated willingness to comply with all study procedures and availability for the duration of the study.Male or female, aged 4–10 years inclusive.Diagnosis of 100% dorsally translated metaphyseal fractures of the radius with any or no distal ulna involvement near the same level in the ipsilateral arm (AO Classification of Long Bone Fractures 23-M/3.1, 23-M/3.2, 23rM/3.1, 23rM/3.2).Fracture is less than 5 cm from the distal radial growth plate.Fracture is acute (occurred less than 10 days prior to consent and assignment of treatment arm AND with ability to be taken to operating room (OR) or reduced in the emergency department (ED)).Willing to adhere to the immobilisation regimen.Exclusion criteriaPhyseal involvement of fracture.Presence of fractures other than the ulna near the same level in the ipsilateral arm.Presence of pathologic fracture or open fracture.Metabolic or neuromuscular diagnosis, or bone disease.Patient and parent or legal guardian are unable to adhere to procedures or complete follow-up due to insufficient comprehension of consent form or surveys or developmental delay.Patient and parent or legal guardian not fluent in English or Spanish.Patient is a ward of the state.

### Interventions

The study interventions investigated herein are a direct comparison of reduction under sedation of paediatric distal radius fractures versus simple immobilisation. Based on a recent survey study, reduction under sedation is the most commonly employed and recommended treatment pathway, likely due to concerns for long-term functional consequences due to fixed deformity.^8^ Simple immobilisation without attempted reduction is often employed by a significant portion of surgeons surveyed based on previous studies showing significant remodelling potential of these overriding fractures and no difference in functional outcomes at 1 year after injury. Simple immobilisation avoids the need for sedation and avoids the risk of re-displacement, which may occur after reduction. Comparison of the two treatments does not involve investigational drugs, biologic pharmaceuticals or devices. A reduction procedure is accompanied by various levels of deep sedation in the emergency department or operating room setting. For immobilisation without reduction, surgeons may provide pain medication to facilitate the casting procedure. Analgesia should seek to enhance the comfort of the child, though should not intentionally alter their conscious level/responsiveness using the American Association of Anesthesiologists Definition of General Anesthesia and Levels of Sedation/Analgesia.

Both treatment arms involve one-time administration of a fracture treatment by a physician or physician extender. Adherence to the intervention will be defined as receiving only the treatment procedure to which the participant was originally randomised. Non-adherence or cross-over for this study is defined as when a patient is randomised to one treatment arm but receives the procedure for the other. Concomitant medications, supplements, complementary or alternative therapies, treatments or procedures will be allowed after participant randomisation to one of the two treatment arms with the approval of the treating surgeon. This means that later surgery, subsequent manipulation or any other care decision is completely unconstrained by the trial and will be recorded. Medications or therapies that a patient is undergoing prior to the injury are allowed to continue. The type of immobilisation is per surgeon discretion and will be documented. Immobilisation can include long arm cast, short arm cast and splints per the surgeons’ discretion. Any changes in immobilisation or additional procedures will be documented and analysed in the post hoc analysis.

### Randomisation

In an attempt to reduce serious imbalance in baseline covariates believed to be prognostic of the primary outcome and preserve treatment allocation randomness, patients will be randomised via a minimal sufficient balance (MSB) algorithm.^17^ Briefly, when the next participant is to be randomised, distributions of baseline covariates from previously enrolled participants will be compared between treatment arms. The three variables included in the MSB algorithm will be hospital site, sex and age (continuous). A voting scheme, incorporating measures of imbalance for all covariates of interest, will determine whether the next participant is randomised with simple randomisation or with a biased coin assignment. If any covariate crosses the threshold for imbalance and randomising the participant to a particular arm will reduce imbalance, the participant will be randomised with a biased coin probability to that arm. As participants need to be randomised in real time, randomisation will occur through the Research Electronic Data Capture (REDCap) platform managed by the DCC. Data entry triggers will be used to execute an external SAS program to pull data from the REDCap project, run the MSB algorithm and assign the participant to an arm. The SAS program will then push the assignment back into REDCap.

### Sample size considerations

Sample size calculations were based on detecting a clinically meaningful difference in the Patient-Reported Outcomes Measurement Information System (PROMIS) Pediatric Computer Adaptive Test (CAT) V.2.0 - Physical Function - Upper Extremity (UE) of 4 points. PROMIS measures use a T-score metric with a mean of 50 and SD of 10 in a reference population.^18^ A sample size of 133 per arm, assuming a two-sided type I error rate of 0.05, will provide 90% power to detect a difference between arms of 4 points. To conservatively account for 20% lost to follow-up or missing data on the primary outcome at 12 months, we have inflated our sample size to 167 per arm, for a total target enrolment of 334.

### Interim analysis

No interim analyses are planned for efficacy or futility. An interim analysis for sample size re-estimation is planned to allow for modifications to the planned sample size, accounting for uncertainty in the initial design assumptions. Specifically, a blinded sample size re-estimation based on the SD of the primary outcome will be performed after the first 100 participants have completed the 6-month follow-up. The DCC unblinded statistical team will obtain an estimate of the within-group SD using the 6-month assessment of the primary outcome. The decision to increase the sample size, if the observed SD is larger than the SD assumed during trial planning, will be based only on the preliminary estimate of the SD and not on preliminary estimates of treatment effect. This approach to sample size re-estimation allows for sample size adjustment based on the observed interim variance compared with the pretrial variance, without affecting type I error. The target enrolment may be increased accordingly, after review by the steering committee. No formal interim analyses for efficacy or futility will be planned. The Data and Safety Monitoring Board (DSMB) will review data summarisations on adverse events and primary response variables both overall and by study arm. The DSMB may request additional formal interim safety summaries for harm to help inform decisions and recommendations. There will be no formal stopping guidelines and decisions to suspend or discontinue the trial will be based on DSMB recommendations.

### Outcomes

The primary outcome of interest is the PROMIS Pediatric CAT – Upper Extremity measured at 1 year (table 1). The measure is a validated patient-reported outcome for function that is correlated with physiological tests of function.^18^ Secondary outcomes of interest include additional measures of perceived pain captured by the Disabilities of the Arm, Shoulder and Hand – Sports / Performing Arts Module (DASH S/PA), PROMIS Pediatric V.2.0 - Pain Interference, Wong-Baker FACES pain score, and PROMIS Pediatric V.1.0 Global Health (7+2). Cosmesis (assessed by parent rating of appearance), complications, missed work (parents) or school, parent-reported satisfaction, radiographic angulation, and occurrence/number of revisions, refractures, re-reductions and reoperations will also be assessed.

**Table 1 T1:** Outcome measures and time points of analysis

	Measure	Time-point	
Primary	PROMIS Pediatric CAT V.2.0 – Physical Function – Upper Extremity^19^	1 year	
Secondary	PROMIS Pediatric CAT V.2.0 – Physical Function – Upper Extremity	6 weeks, 3 months, 6 months	
	DASH – S/PA^20^	6 weeks, 3 months, 6 months, 1 year*	
	PROMIS Pediatric V.2.0 - Pain Interference^19^	6 weeks, 3 months*, 1 year	
	Wong-Baker FACES Pain score^21^	6 weeks, 3 months*	
	PROMIS Pediatric V.1.0 - Global Health (7+2)^22 23^ – Global Score	6 weeks, 3 months, 6 months, 1 year*	
	PROMIS Pediatric V.1.0 - Global Health (7+2)^22 23^ – Fatigue interference	6 weeks, 3 months, 6 months, 1 year	
	PROMIS Pediatric V.1.0 - Global Health (7+2)^22 23^ – Pain interference	6 weeks, 3 months, 6 months, 1 year	
	Number of revisions, refractures, reductions and reoperations	1 year*	
	Other complications	1 year	
	Missed work or school	3 months*	
	Satisfaction questionnaire^6^	3 months, 6 months*, 1 year	
	Cosmesis	6 weeks, 3 months, 6 months, 1 year*	
	Radiographic alignment	6 weeks†	

* Indicates time point of clinical interest incorporated in family of hypothesis tests with adjustment for multiplicity.

† Radiographic is only collected as part of standard of care and is only mandated at the 6-week visit.

CAT, Computer Adaptive Test; DASH – S/PA, Disabilities of the Arm, Shoulder and Hand – Sports/Performing Arts Module; PROMIS, Patient-Reported Outcomes Measurement Information System.

The statistical methods detailed here focus on analyses incorporating outcomes measured through 1 year. Exploratory objectives beyond 1 year will be detailed elsewhere.

### Analysis populations and estimands

Primary analyses will be based on an intention-to-treat (ITT) principle (treatment policy estimand) and will include all participants randomised. For the treatment policy estimand, participants will be analysed according to their randomised treatment assignment. Anticipated intercurrent events include treatment cross-over, withdrawal from study or lost to follow-up. Outcomes collected after treatment cross-over will be included in the analysis regardless of this intercurrent event, to align with the ITT analysis. Outcomes that are missing due to withdrawal, lost to follow-up or other reasons will be handled as described below. A sensitivity analysis will be based on a per-protocol population, to assess the robustness of the ITT analysis. The per-protocol (adherence estimand) population will be defined as all randomised participants who receive their intended intervention. If a participant crosses over to the alternative treatment during the follow-up period, this participant will be included in their allocated arm, but follow-up will be censored at the time of treatment cross-over. Thus, only outcomes collected prior to treatment cross-over will be included.

### Statistical analyses

Descriptive statistics will summarise demographics, medical history, baseline outcome measures and other clinical characteristics by arm. The participant disposition will be summarised using frequencies and proportions for all ITT participants. The study will follow Consolidated Standards of Reporting Trials guidelines for reporting results.

Analysis for the primary aim will use a mixed-effect model for repeated measures of the primary outcome, PROMIS Pediatric CAT – Upper Extremity, measured at baseline (reflecting preinjury status), 3 months, 6 months and 1 year. The model will include fixed effects for treatment arm, time as a categorical variable, and the treatment arm by time interaction term. Sex and age (continuous) will be included as covariates. Incorporation of a random centre effect will allow for separation of between-site and within-site variance components. For the repeated measures within a participant, we will assume an unstructured covariance matrix. If the model does not converge, then a simpler covariance structure (compound symmetry) will be used. We will report estimates for the mean and SD at 1 year for each arm. The between-arm difference in model-estimated 1 year means will be reported with corresponding 95% CI and p value. The primary analysis will be assessed using a two-sided type I error rate of 0.05, with no adjustment for testing of secondary or exploratory outcomes. Two sensitivity analyses will be conducted including a per-protocol analysis and analyses using multiple imputation for missing data, as described below. Model validity will be assessed via residual diagnostics. We will graphically assess the distribution of residuals to determine if there is gross departure from normality, and if so, transformations may be considered. The unstructured covariance matrix allows for differential variance across time points. If there is evidence of a differential variance between treatment arms, then the covariance matrix may be estimated separately for each arm.

Secondary analyses will incorporate a similar modelling strategy for all continuous repeated measures outcomes. A generalised linear mixed-effect (GLMM) model will be fit for binary and count outcomes with appropriate distributional assumptions and link functions. Specifically, Poisson loglinear GLMM models will be fit for the number of missed school days and number of missed work days of the parent(s). Logistic GLMM models will be fit for parent satisfaction, defined as parents who reported being at least somewhat satisfied, and for occurrence of revisions, refractures, re-reductions and/or reoperations. A false discovery rate correction will be applied to account for multiplicity within the prespecified family of hypothesis tests at key clinical time points for each secondary outcome (table 1). P values for additional time points and all additional exploratory analyses will not be adjusted for multiplicity.

Planned subgroup analyses of the primary outcome may include assessment of treatment effects by age group and sex. Specifically, models will be fit with interactions between the treatment arm and each of these variables. Although we anticipate being underpowered for these specific interactions, these models will be used to assess whether there is evidence that the effect of the intervention is different depending on these prespecified subgroups.

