### Missing data

Every effort will be made to minimise missing data for assessment in participants who have not withdrawn from the study. For the main analysis, we will use a mixed model for repeated measures analysis, including all available measurements of the response variable collected at 3 months, 6 months and 1 year as well as the fixed and random effects specified above. This model assumes that data are missing at random, conditional on the measurements included in the model.

Mechanisms of missing data will be examined, and if appropriate, sensitivity analyses will be performed using multiple imputation methods. Specifically, we will use a fully conditional specification for linear mixed models method to impute incomplete longitudinal outcomes. This approach assumes that missingness is at random, conditional on the variables included in the imputation model. Should there be reason to believe the data are not missing at random, sensitivity analyses will be considered with multiple imputations using the delta-adjustment approach.

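### The primary model's response times are stated in two ways, and under neither is the 1-year difference adjusted for the pre-injury PROMIS score

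*Protocol article*

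**What the plan says.** The Statistical analyses section of the protocol article describes a repeated-measures mixed model for the PROMIS upper-extremity score "measured at baseline (reflecting preinjury status), 3 months, 6 months and 1 year". On its terms it says: "The model will include fixed effects for treatment arm, time as a categorical variable, and the treatment arm by time interaction term". The only covariates named are sex and age. There is a random centre effect, and the within-child covariance is unstructured, with compound symmetry as the fallback. The primary contrast is the difference in model-estimated 1-year means.

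The Missing data section describes the same main analysis as "including all available measurements of the response variable collected at 3 months, 6 months and 1 year", together with the fixed and random effects already listed. It adds no term for the baseline score. It then assumes that data are missing at random given the measurements in the model.

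The Analysis populations and estimands section says that the primary analyses "will include all participants randomised".

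**The concern.** The article fixes response times, fixed effects, covariates and covariance for its primary test, so this is not detail left to an analysis plan. Two points follow.

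First, the two sections disagree on whether baseline is a response. The choice decides whether a child with only a baseline score enters the model, and which measurements the missing-at-random assumption conditions on.

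Second, a reader could suppose that putting baseline in the response vector adjusts for it. It does not when each arm has its own baseline mean. In that case a chance difference at baseline is absorbed by the arm terms and does not inform the 1-year contrast. Randomisation balances site, sex and age but not pre-injury function, so nothing else in the design removes that source of variation. What is at stake is precision that a score already collected could supply.

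**Working it through.** **Inputs.** All come from Sample size considerations: 133 evaluable children in each arm, a two-sided 5% test, a target power of 90% at 4 points, and SD 10, taken from the statement that "PROMIS measures use a T-score metric with a mean of 50 and SD of 10 in a reference population". The correlation ρ between pre-injury and 1-year scores is not given, so 0.1, 0.3 and 0.5 are assumed. The calculation leaves out age, sex and centre. Strictly, ρ should be the partial correlation given those terms.

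**The plan's own figure.** The normal approximation n = 2 × 10² × (1.960 + 1.282)² / 4² gives 132 per arm. The exact two-sample t calculation gives 133, with power 90.1%. Allowing for 20% loss, 133 / 0.80 = 166.25, rounded up to 167 per arm, or 334 in all. The stated sizes reproduce, and they rest on an unadjusted SD.

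**Variance of the 1-year contrast, complete data, 133 per arm.** The raw difference in means has variance 2 × 10² / 133 = 1.504. Generalised least squares for the repeated-measures model gives:
- baseline as a response with free arm means (Statistical analyses): 1.504
- baseline omitted (Missing data): 1.504
- baseline as a covariate, or as a response with arm means constrained equal: 1.504 × (1 − ρ²)

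With SE = √variance, half-width = 1.96 × SE and power = Φ(4/SE − 1.96):

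| ρ (assumed) | Variance | SE | 95% CI half-width | Power at 4 points |
|---|---|---|---|---|
| no adjustment | 1.504 | 1.226 | 2.40 | 90.4% |
| 0.1 | 1.489 | 1.220 | 2.39 | 90.6% |
| 0.3 | 1.368 | 1.170 | 2.29 | 92.8% |
| 0.5 | 1.128 | 1.062 | 2.08 | 96.5% |

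A simulation of 4,000 trials at ρ = 0.5, with the baseline slope estimated, gave an adjusted-to-unadjusted variance ratio of 0.74, against 1 − 0.5² = 0.75.

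**With missing data.** Take 167 per arm, 20% lost straight after baseline, and ρ = 0.5. The variance is 1.497 with baseline omitted, 1.422 with baseline as a free response, and 1.123 with either form of adjustment. The free-response model therefore recovers 1 − 1.422/1.497 = 5% of the variance, and adjustment recovers 1 − 1.123/1.497 = 25%. The two adjusted forms had equal variance in every scenario computed.

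**The case against.** The strongest reply is that nothing the protocol promises fails. The contrast is unbiased under randomisation, and its standard error already allows for chance baseline imbalance. The 90% power is calculated on an unadjusted SD, and the Interim analysis section lets enrolment rise if the SD proves larger. All of this stands. A reader might infer that the primary analysis is biased or the trial too small, and the documents support neither.

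The gain may also be small. The score describes an earlier state and is obtained after the injury, in children whom the article calls healthy, so it may be imprecise or have little spread. At ρ = 0.1 the benefit is negligible. Part of any correlation may already be taken up by age, sex and centre. This stands too, and it is why no single figure should be claimed and no large saving in patients asserted.

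The mismatch between the sections has little numerical effect by itself. With complete data both versions give 1.504. In the missing-data case above the standard errors differ by about 2.5% (√1.422 = 1.192 against √1.497 = 1.224). The Missing data section may simply be listing follow-up visits. That limits the consequence, but the primary model is still stated in two ways.

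A reader might also infer that the Missing data version is disqualified because it gives no weight to children without a follow-up score, although all randomised participants are to be included. That goes too far: a standard baseline-as-covariate model leaves out the same children, and the populations section itself defers missing outcomes to the later section. Finally, the documents do not say whether baseline is completed before assignment is known, so no defect can be read into its timing.

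**Conclusion.** The point holds as a contradiction in wording plus an efficiency that is free to take. The two sections give different response vectors for the primary model, and neither adjusts the 1-year difference for the pre-injury score. Validity, type I error and the stated sample size are not in question.

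The size depends on an undocumented correlation. The variance reduction is about 1%, 9% or 25% at ρ = 0.1, 0.3 or 0.5, assuming SD 10, 133 evaluable per arm and a correlation that is net of age, sex and centre. The contradiction and the absence of adjustment are certain from the text, but the amount gained is not. The severity is that of a worthwhile improvement with two sections to reconcile, not of an error that must be corrected for the trial to stand.

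**What to change.** State one model, in the same words, in Statistical analyses and Missing data.

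- **Preferred:** keep baseline, 3 months, 6 months and 1 year as responses, but constrain the arm means to be equal at baseline, so that arm effects appear only at the post-baseline visits. Children with only a baseline score then stay in the model, in line with the inclusion of all randomised participants.
- **Alternative:** use 3 months, 6 months and 1 year as responses, with baseline score and baseline-by-time as covariates. Say openly that children with no post-baseline score then contribute nothing.

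The contrast remains the difference in 1-year means, and the sample size need not change. The cost is wording in the protocol and in any analysis plan, settled before outcome data are compared by arm. It needs no new data and no additional participants.
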